## Abstract

**Background:**

Infertility is one of the most important and underappreciated reproductive health problems in developing countries. Currently, in vitro fertilization and embryo transfer is the most effective treatment strategy for infertility. In a frozen-thawed cycle, single-blastocyst transfer can not only ensure relatively higher pregnancy and live birth rates but also effectively reduce the risk of maternal and neonatal complications. In frozen-thawed cycles, progesterone is initiated to promote the final phase of endometrial preparation prior to embryo transfer. However, the optimal duration of exposure to progesterone has remained inconclusive. Therefore, we designed a randomized controlled trial (RCT) to compare the effects of different prolonged progesterone transformation times (P+6 and P+7) on the pregnancy outcomes of D6 single blastocyst transfer in a frozen-thawed cycle.

**Methods:**

This is a single-center, prospective, randomized controlled clinical trial involving 900 patients with single blastocyst transfer in the frozen-thawed cycle, aged from 20 to 38 years, with less than three transfers, and with HRT-cycle single D6 blastocyst transfer in the current cycle. Participants will be randomly assigned (1:1) into two parallel groups: the transfer of day 6 blastocysts on the 7th day of progesterone supplementation and the transfer of day 6 blastocysts on the 6th day of progesterone supplementation. The primary outcome measure is the clinical pregnancy rate. Secondary outcome measures include the miscarriage rate and live birth rate.

**Discussion:**

This is the first randomized controlled trial to compare the transfer of day 6 blastocysts on the 6th and 7th day of progesterone supplementation. The results of this study will provide evidence for whether to prolong the duration of exposure to progesterone prior to embryo transfer.

**Trial registration:**

ClinicalTrials.gov, ID: NCT04938011. Registered on 19 June 2021.

**Supplementary Information:**

The online version contains supplementary material available at10.1186/s13063-022-07013-1.

## Administrative information

Note: the numbers in curly brackets in this protocol refer to SPIRIT checklist item numbers. The order of the items has been modified to group similar items (see http://www.equator-network.org/reporting-guidelines/spirit-2013-statement-defining-standard-protocol-items-for-clinical-trials/).

## Introduction

### Background and rationale {6a}

Assisted human reproductive technology (ART) has undergone more than 40 years of development and has been increasingly used worldwide. The number of embryos transferred is often increased to improve clinical pregnancy rates, which also increases the risk of multiple pregnancies [1]. Therefore, single blastocyst transfer has become an important method to achieve safer ART. Compared with cleavage-stage embryos, blastocysts undergo a reselection process that spans the 8-cell-stage developmental block and eliminates embryos with poor developmental potential. Moreover, blastocyst transfer is more synchronized with endometrial development, and consequently, the pregnancy outcomes of fresh-cycle blastocyst transfer are superior to those of cleavage-stage embryos [2, 3]. Especially with the continuous improvement of vitrification technology, in a frozen-thawed cycle, single blastocyst transfer can not only ensure relatively higher pregnancy and live birth rate (LBR) but also effectively reduce the incidence of ovarian hyperstimulation syndrome, multiple birth rates, and fetal and maternal risk [4, 5].

The development rate of embryos from the cleavage stage to the blastocyst stage is not uniform, and blastocysts may form on days 5, 6, and 7 after fertilization. The implantation potential of blastocysts formed at different timing and its impact on pregnancy outcomes are still controversial [6]. In studies on fresh cycles, the pregnancy rate of D5 blastocysts was superior to that of D6 blastocysts, suggesting that the rate of blastocyst development predicts the implantation potential of the embryo [7, 8]. However, there is controversy regarding the clinical outcomes of D5 or D6 blastocyst transfer in frozen-thawed blastocyst transfer cycles. Frozen-thawed cycles ensure consistency of endometrial development and allow a better analysis of the impact of the blastocyst development rate on pregnancy outcomes. Recently, retrospective cohort studies concluded that the clinical pregnancy, implantation, and LBR after frozen-thawed blastocyst transfer are significantly higher in D5 embryos than in D6 embryos [9, 10]. However, some studies found no significant difference between day 5 and day 6 frozen-thawed blastocysts, with similar clinical pregnancy, implantation, and birth rates [11, 12].

Although the clinical outcomes of day 5 and day 6 frozen-thawed blastocyst transfers are still under discussion, this does not mean that the freezing of D6 blastocysts will be abandoned. For a proportion of patients with low ovarian function, poor embryo quality, the inability to tolerate another in vitro fertilization cycle, or other reproductive issues, the transfer of D6 blastocysts can still achieve a certain clinical pregnancy rate and thus a satisfactory pregnancy outcome, solving the patients’ dilemmas. The key to achieving successful implantation of frozen embryo transfer (FET) is the synchronous development of the embryo with the endometrium that shows embryo receptivity [13]. The human endometrium is receptive for only a relatively short period of time with strict temporal and spatial limitations, typically on days 20–24 of the menstrual cycle, which also corresponds to days 7–11 after the LH surge [14]. Compared with the D5 endometrium, the D6 endometrium is less receptive to embryos [15]. Thus, a proper assessment of the optimal endometrial preparation is the primary way to maximize the outcomes of FET [16].

Hormone replacement therapy (HRT) achieves artificial adjustment of the opening of the implantation window by mimicking the estrogen and progesterone changes in normal human menstrual cycles with exogenous hormones. Prolonging the time of endometrial transformation by progesterone in the FET cycle can reduce uterine contractions, enhance endometrial receptivity, and shorten the time interval between development and implantation after embryo implantation. Recent data from transcriptomic microarray and simple histologic endometrial dating have shown that delayed endometrial development in the luteal phase occurs in up to approximately 25% of the general population and, therefore, postponing the day of embryo transfer [17, 18]. However, existing studies of frozen-thawed blastocyst transfer cycles have focused more on the impact of different blastocyst qualities on pregnancy outcomes, and there is little research on the timing of D6 single blastocyst transfer. Currently, most blastocysts are usually transferred on the 6th day of progesterone supplementation, but the optimal duration of exposure to progesterone remains inconclusive. A recent RCT compared the outcomes of blastocyst transfer on the 5th or 7th day of progesterone administration, and the LBR tended to favor the 5th day of progesterone administration, although statistical significance was not shown [19]. However, a recent retrospective cohort study reported that day 6 blastocysts had nonsignificantly higher LBR when transferred on the 7th day of progesterone administration [20]. This randomized controlled study was conducted to compare the effects of different prolonged progesterone transformation times (P+6 and P+7) on the pregnancy outcomes of D6 single blastocyst transfer in frozen-thawed cycles.

### Objectives {7}

The objective is as follows: to compare the pregnancy outcomes by randomizing the transfer of a single day 6 blastocyst to the 6th day or 7th day of progesterone supplementation.

### Trial design {8}

This is a single-center, prospective, randomized controlled study. The type of this trial design is parallel group, it is also superiority trial, and the allocation ratio between the control group and the experimental group is 1:1.

## Methods: participants, interventions, and outcomes

### Study setting {9}

Patients are being recruited from the Affiliated Drum Tower Hospital of Nanjing University Medical School, China. This study has been approved by the ethics committees (listed in Additional file1).

### Eligibility criteria {10}

#### Inclusion criteria

Women aged 20 to 38 yearsThose with less than three transfer cyclesThose undergoing an HRT frozen-thawed cycle with a single day 6 blastocyst transfer in the current cycleThose who consent to participate in this study and sign the informed consent form

#### Exclusion criteria

A chromosomal abnormality in either the patient or their partnerContraindications to HRTPatients with intramural myoma affecting the morphology of the uterine cavity, severe adenomyosis, endometriosis, congenital uterine anomalies, endometrial tuberculosis, intrauterine adhesion, and other diseases significantly affecting embryonic implantationContraindications to HRTPatients currently participating in other clinical studies

### Who will take informed consent? {26a}

Prior to study enrollment, study staff will provide participants with verbal and written information about the study in plain language. Participants will be given ample time to ask questions, and the couples will be asked to provide written consent if they agree to be part of the study.

### Additional consent provisions for collection and use of participant data and biological specimens {26b}

No additional consent will be collected.

## Interventions

### Explanation for the choice of comparators {6b}

The extended day is theoretically also covered by the implantation window. However, the results of the current D6 day embryo are not satisfactory, possibly because of the problem of synchronization and communication between the embryo and the endometrium. Additionally, the current tendency in assisted reproduction is to prolong the time of in vitro embryo culture to obtain more developed embryos, identify an implantation window for these mature embryos, and further increase the success rate of assisted reproduction.

### Intervention description {11a}

A total of 900 participants will be enrolled and equally randomized into two parallel treatment armsA)Progesterone + 7 (P+7): the transfer of day 6 blastocysts on the 7th day of progesterone supplementationB)Progesterone + 6 (P+6): the transfer of day 6 blastocysts on the 6^th^ day of progesterone supplementation

#### Endometrial preparation

All the included patients will undergo an HRT cycle for endometrial preparation. Treatment will start on day 2 or day 3 of menstruation with oral Femoston (estradiol 2 mg po tid). After approximately 10–12 days of estrogen treatment, a transvaginal ultrasound will be performed to measure the endometrial thickness. Two procedures for further treatment depending upon the endometrial thickness are listed as follows:If the endometrium thickness is not less than 8 mm, patients will continue to take Femoston (estradiol tablet). On days 16–20 of the HRT cycle, patients will be changed over to receive oral Femoston (2 mg estradiol and 10 mg dydrogesterone tablet, po tid) and intramuscular injections of progesterone (60 mg qd) to transfer the endometrium into the secretory phase.If the endometrium thickness is less than 8 mm, the dose of oral Femoston (estradiol tablet) will increase to 8 mg until the endometrium thickness reaches 8 mm. On days 18–20 of the HRT cycle, Femoston (2 mg estradiol and 10 mg dydrogesterone tablet, po tid) and progesterone (60 mg qd) will be administered to transfer the endometrium into the secretory phase. If the endometrium thickness is still less than 8 mm, it should be discussed with patients whether to proceed with FET or abandon the protocol.

#### Frozen-thawed embryo transfer

*Group A*: the transfer of day 6 blastocysts on the 7th day of progesterone supplementation
*Group B*: the transfer of day 6 blastocysts on the 6th day of progesterone supplementation

#### Corpus luteum support

Estradiol valerate will be stopped gradually after 8 weeks of FET; vaginal progesterone gel or oral dydrogesterone will be continued for 8 weeks of FET.

#### Follow-up evaluation

Detection of serum β-hCG 12-14 days after embryo transferUltrasound examination 30 days after embryo transfer to examine the intrauterine gestational sac with a fetal heartbeat. The flow chart of this study is shown in Fig.1.

**Fig. 1 Fig1:**
[figure not shown]
Study flowchart

### Criteria for discontinuing or modifying allocated interventions {11b}

#### Withdrawal criteria

Patients will not be suitable to continue the follow-up study if they have any of the following conditions:Failure to comply with the program requirements for treatmentUnexpected withdraw from transplantationThe use of other drugs that may affect embryo implantation in the study

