### Outcomes {12}

#### Primary outcome measure

The primary outcome measure is the clinical pregnancy rate: the ratio of the clinical pregnancy (intrauterine gestation sac with a fetal heart beat) number to the number of patients who received embryo transfer.

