### Sample size {14}

The sample size calculation is based on the clinical pregnancy rate. Retrospective data analysis (from January 2019 to December 2020, a total of 490 cycles of D6 single blastocyst transfer) showed that the clinical pregnancy rate of D6 single blastocyst transfer was approximately 49%. In our present study, we hope to improve the clinical pregnancy rate to 60%, the two-sided significance level will be set at *α* = 0.05, and the statistical power will be calculated as 1 − *β* = 0.90. The ratio between groups will be 1:1. The number of samples required for each group is 430. According to the 5% loss rate, there should be no fewer than 450 participants in each group, for a total of 900 participants.

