## Assignment of interventions: blinding

### Who will be blinded {17a}

This study is an open trial. Both patients and researchers know the group assignments in the trial and only the statisticians are blinded to the grouping.

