### Methods in analysis to handle protocol non-adherence and any statistical methods to handle missing data {20c}

Data will be analyzed following the ITT principle. Missing data will be analyzed. The imputation of missing values is not intended, although multiple imputations might be used within sensitivity analyses assuming data are missing at random.

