### Adverse event reporting and harms {22}

Adverse events (AEs) are defined as any untoward or unfavorable medical occurrences associated with the subject’s participation during the research. AEs in this study will be divided into study-related AEs and non-study-related AEs, which will be judged by clinicians at the time of recording. AEs related to the study will include hepatic injury and thrombosis. AEs related to Femoston and progesterone include nausea, dizziness and headache, fatigue, measles, breast swelling, menorrhagia or amenorrhea, hepatic dysfunction, edema, and weight gain.

All AEs will be recorded in detail. Once any adverse reaction occurs during medication use, the drug will be stopped immediately. Serious AEs will be reported to the principal investigator immediately, and appropriate measures will be initiated instantly. The ethics committee will determine whether the AE is likely to have been associated with the experimental drug and whether it is necessary to break the blinding codes.

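### The withdrawal rule ends follow-up for non-adherent women and the outcome counts only transferred women, which contradicts the stated ITT analysis

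*Protocol article*

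**What the plan says.** All references are to the protocol article.

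- **Withdrawal criteria, in {11b}:** "Patients will not be suitable to continue the follow-up study if they have any of the following conditions". Three conditions follow: not complying with the treatment programme, unexpectedly withdrawing from the transfer, and taking other drugs that may affect implantation.
- **Suspension criteria, in {11b}:** the patient's request, safety reasons such as treatment-related adverse events, and loss to follow-up or incomplete data. The section does not say what suspension entails.
- **Handling of non-adherence and missing data, {20c}:** "Data will be analyzed following the ITT principle". Then: "The imputation of missing values is not intended, although multiple imputations might be used within sensitivity analyses assuming data are missing at random".
- **Outcomes, {12}:** the denominator of the primary outcome is "the number of patients who received embryo transfer". The live birth rate uses the same denominator.
- **Blinding, {17a}:** "Both patients and researchers know the group assignments in the trial". Only the statisticians are blinded.
- **Table 1:** randomisation is on the day progesterone starts, before transfer. Medical record review is scheduled at 30/42 days after transfer and after delivery.

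**The concern.** ITT analysis needs two things: every randomised woman in the denominator of her allocated arm, and an outcome or a fixed rule for each of them. The plan undercuts both. The withdrawal rule stops follow-up for women who deviate, and nothing in the main analysis replaces their outcomes. The outcome definition separately drops women who do not reach transfer.

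Each withdrawal condition can arise after allocation. Staff who know the arm judge compliance and whether another drug matters. The arms differ by one day of progesterone before transfer, so opportunities to deviate need not be equal. If the women removed differ between arms in number or prognosis, the comparison loses the protection of randomisation.

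Much of this missingness is avoidable. A transferred woman who deviated can still have her ultrasound result and delivery record retrieved, and a woman without a transfer has a known result for this cycle. An analysis plan written later cannot recover outcomes that staff were told to stop collecting.

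**Working it through.** **1. The plan's own figure.** Inputs from Sample size {14}: 49% vs 60%, two-sided α = 0.05, power 0.90, ratio 1:1, 430 per group, 5% loss, 450 per group.

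Pooled-variance formula, with p̄ = 0.545:

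n = [1.960·√(2·0.545·0.455) + 1.282·√(0.49·0.51 + 0.60·0.40)]² / 0.11² ≈ 429 per group (stated: 430).

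Inflation: 430/0.95 ≈ 453 (stated: 450). The sample size reproduces closely and is not at fault.

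**2. Who is in the main analysis as written.**

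| Woman | Followed up? | Imputed in main analysis? | In the denominator? |
|---|---|---|---|
| Adherent, transferred | Yes | Not needed | Yes |
| Transferred, did not comply or used other drugs | No (Withdrawal criteria) | No ({20c}) | Yes by definition, but no outcome is secured |
| Withdrew from transfer | No (Withdrawal criteria) | No ({20c}) | No ({12}) |
| Suspended | Not stated | No ({20c}) | Not stated |

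Only the first row is certain to contribute.

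**3. Possible bias under no true effect.** The documents give no removal rates by arm, so these rates are assumptions. Let the true rate be 0.49 in both arms with 450 randomised per arm. A share x is removed from an arm, and the removed women have pregnancy rate r. The observed rate is (0.49 − x·r)/(1 − x).

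Example, 5% removed in P+6, 10% in P+7, r = 0:
- P+6: 0.49/0.95 = 0.516; P+7: 0.49/0.90 = 0.544; difference 2.9 points.
- SE = √(0.516·0.484/427.5 + 0.544·0.456/405) = 0.0346.
- Rejection probability at ±1.96 ≈ 0.13.

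| Removed, P+6 vs P+7 | Spurious difference, r = 0 | Type I error, r = 0 | Type I error, r = 0.25 | Type I error, r = 0.49 |
|---|---|---|---|---|
| 2% vs 5% | 1.6 points | 0.075 | 0.056 | 0.05 |
| 3% vs 7% | 2.2 points | 0.097 | 0.061 | 0.05 |
| 5% vs 10% | 2.9 points | 0.13 | 0.069 | 0.05 |

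With r = 0.49 removal is unrelated to outcome and there is no bias. Equal removal of 5% in both arms with the same r also gives 0.05. Swapping the arms reverses the sign of the difference.

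**4. Sensitivity of one illustrative result at the planned loss.** 5% of 450 is about 23, leaving 427 per arm. The counts are chosen for illustration; the test is the uncorrected χ².

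| Handling of the 23 lost per arm | P+6 | P+7 | p |
|---|---|---|---|
| Left out | 209/427 (48.9%) | 247/427 (57.8%) | 0.009 |
| Counted as not pregnant | 209/450 (46.4%) | 247/450 (54.9%) | 0.011 |
| Extreme bound: all lost P+6 pregnant, no lost P+7 pregnant | 232/450 (51.6%) | 247/450 (54.9%) | 0.32 |

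**5. Power.** With equal removal of 5%, 10% or 15%, the complete-case analysis at 49% vs 60% has power 0.899, 0.883 or 0.865. Keeping all 450 per arm and counting removed women as not pregnant (at 5%: 46.5% vs 57.0%) gives 0.882, 0.845 or 0.804. The issue is validity, not power.

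**The case against.** **The wording is ambiguous.** The criteria sit under a heading about changing allocated treatment, and the phrase about follow-up could mean the later part of the trial. No section says that collected data are discarded. This is fair, but the sentence names follow-up, and nothing elsewhere says that outcomes are still collected after withdrawal. Staff who follow it literally would stop.

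**Suspension and adverse events.** A reader might infer that suspended women, or women whose drug is stopped, also leave follow-up. The documents do not support that. The Suspension criteria state no consequence, and {22} says only "Once any adverse reaction occurs during medication use, the drug will be stopped immediately", which concerns the drug. Suspension may add to the problem and needs clarifying; it is not an established route of removal.

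**An ITT analysis is still possible.** A reader might infer that it cannot be done. That is too strong. Record review is already scheduled, and multiple imputation is already foreseen, though only as an option for sensitivity analyses. What stands is that none of these is fixed as the main analysis.

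**The extreme case is not realistic.** Women who withdraw from transfer cannot be pregnant from this cycle's embryo, so p = 0.32 is a bound and not a forecast. Two milder checks agree: with 14 vs 9 pregnancies among the lost women (223/450 vs 256/450), p = 0.027. At the design rate of 60% in P+7 (256/427), the p-values for the three handlings are 0.0012, 0.0017 and 0.11. The time from randomisation to transfer is also short, which limits withdrawals before transfer.

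**This belongs in an analysis plan.** That holds for the detail of sensitivity analyses. It does not hold for a collection rule or an outcome denominator, which the protocol itself fixes.

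**Conclusion.** The contradiction is real. The Withdrawal criteria and the transfer-only denominators select on events after randomisation, while {20c} promises ITT without imputation in the main analysis. As written, the main comparison is of adherent, transferred women with observed outcomes.

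The consequence cannot be quantified from the documents: the 5% in the sample size section is an overall loss, not a removal rate by arm. Bias is absent if removal is unrelated to outcome, or is equal and alike in both arms. Under the assumed unequal removals, and removed women with a pregnancy rate of 0 to 25%, type I error is about 0.06 to 0.13. In the illustration at 5% loss, counting lost women as not pregnant moves p only from 0.009 to 0.011; significance is lost only towards the extreme bound. The case for change therefore rests on the contradiction and the avoidable loss of outcomes, not on a demonstrated large bias.

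**What to change.** 1. Reword the Withdrawal and Suspension criteria so that they govern the allocated treatment only, and state what suspension means. Whether treatment stops is for the clinical team; the point here is data collection.
2. State that pregnancy and birth outcomes are collected for every randomised woman unless she withdraws consent for data. Remove incomplete data as a reason for suspension. Retrieve outcomes of women already withdrawn through the scheduled record review.
3. Change the denominators of the clinical pregnancy rate and the live birth rate to all randomised women in their allocated arm. Count a woman without a transfer, or with an unobtainable outcome, as not pregnant (and as having no live birth).
4. Keep the per-transfer or per-protocol analysis as supportive.
5. Make the multiple imputation already mentioned in {20c} a firm sensitivity analysis, with best-case and worst-case bounds.

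Cost: an amendment through the ethics committee and registry, a few record look-ups in the centre's own system, a little more analysis, and slightly lower observed rates and power (about 0.88 instead of 0.90 at 5% loss).
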